### Same size and power calculations

Assuming, in line with previous work on interventions to improve mental health literacy in other occupational groups [21], a difference of 0.73 in beliefs about depression treatment between the intervention and control groups at post-intervention, a minimum of 226 participants per group will be required to detect this difference at the nominal 0.05 significance level with 90 % power. For our secondary outcomes, our previous study has shown that 13 % of the working population report suicide ideation [22]. We believe it is realistic to expect a change from 13 % to 8 % prevalence following the trial. Power calculations indicate we will need 267 persons per group to detect this difference at the nominal 0.05 significance level with 80 % power. Assuming 30 % drop-out, we therefore aim to recruit a total of 630 newly unemployed participants over a three month period. This is a feasible and achievable goal, given that approximately 20 unemployed workers lodge a claim each day with Incolink. We will recruit over a period of three months, thus allowing us to obtain a sample size adequately powered to assess both primary and secondary outcomes.

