### Data collection

All participants will complete a baseline electronic survey comprising information on sociodemographic information at the time of study enrolment, knowledge of depression symptoms, attitudes towards those with depression, and stigma, shame, self-blame or social inadequacy. Follow-up surveys will take place immediately post-intervention (six months), and then again at 12 months following enrolment to collect information on changes in knowledge of depression symptoms, attitudes towards those with depression, stigma, shame, self-blame, and social inadequacy and also to assess the impact of the intervention on suicidal ideation and depression symptomatology.

Primary outcome measures will include: scores on the attitudes, beliefs, and help-seeking inhibition subscales of the Depression Stigma Scale (DSS; [10]) and the shame, self-blame and social inadequacy subscales of the Self-Stigma of Depression Scale (SSDS; [16]), and levels of perceived social support from family and friends using the Multidimensional Scale of Perceived Social Support (MSPSS; [17]). Secondary outcomes will include: suicidal ideation as measured by scores on the suicidality subscale of the General Health Questionnarire-28 (GHQ-28; [18]) and depression symptomatology as measured by scores on the Center for Epidemiologic Studies Depression scale-Revised (CESD-R; [19]) and the depression subscale of the Brief Symptom Inventory (BSI; [20]).

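### The two power calculations are not matched to the listed outcomes, so the claim of adequate power for both primary and secondary outcomes is not supported

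*Protocol article*

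**What the plan says.** The section of the protocol article headed Same size and power calculations gives two calculations.

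- **Primary.** Drawing on mental health literacy work in other occupational groups, it assumes "a difference of 0.73 in beliefs about depression treatment between the intervention and control groups at post-intervention". It then says that "a minimum of 226 participants per group will be required" to "detect this difference at the nominal 0.05 significance level with 90 % power". No instrument, unit or SD is given.
- **Secondary.** For suicidal ideation the authors "expect a change from 13 % to 8 % prevalence following the trial", and say that they need "267 persons per group to detect this difference at the nominal 0.05 significance level with 80 % power".

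Allowing for 30% drop-out, the target is 630 (315 per arm). The section closes by describing the recruitment period as "thus allowing us to obtain a sample size adequately powered to assess both primary and secondary outcomes".

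The outcomes are defined under Data collection: "Primary outcome measures will include: scores on the attitudes, beliefs, and help-seeking inhibition subscales of the Depression Stigma Scale", followed by three subscales of the Self-Stigma of Depression Scale (SSDS) and perceived social support on the MSPSS. That makes seven measures if the MSPSS is counted once. The secondary outcome is "suicidal ideation as measured by scores on the suicidality subscale" of the GHQ-28. No threshold is stated. Statistical methods plans multivariate regression for primary and secondary outcomes alike and mentions no binary analysis.

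**The concern.** A power statement tells the reader what a trial can detect on the outcomes it will analyse. Here neither calculation can be read that way.

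The primary calculation concerns beliefs about treatment. No listed outcome is described in those terms. The primary objective speaks of beliefs about depression, and the survey content under Data collection does not mention treatment. The Background reports effects on stigmatising attitudes and on knowledge of treatment as separate findings. Without a scale or SD, the 0.73 cannot be converted into a detectable difference on any listed measure except by working backwards from the stated sample size.

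The secondary calculation compares two proportions, while the outcome is a score. These are different analyses with different power.

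At stake is how the results will be read. A null result on a stigma subscale or on ideation could be taken as informative because the article says that the trial was adequately powered for it.

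**Working it through.** **Inputs from the article:** difference 0.73, 226 per group, 0.05, 90% power; 13% against 8%, 267 per group, 0.05, 80% power; 315 per arm; 30% drop-out. Sidedness is not stated. Two-sided is assumed, with one-sided figures where they help.

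**1. The 226.** It cannot be reproduced, because no SD is given. Solving n = 2(z₁₋α/₂ + z₁₋β)²/d² for d:

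- d = (1.960 + 1.2816) × √(2/226) = 0.305, so the implied SD is 0.73/0.305 = 2.39. One-sided, d = 0.275 and the SD is 2.65.
- If 0.73 were itself a standardised difference, n = 2 × (3.2415/0.73)² = 39.4, or 40 per group. So 226 fits only if 0.73 is in raw points of some scale.

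**2. Why the missing SD matters.** The article gives no SD for any listed scale, so these SDs are assumptions for illustration only. With 220 analysed per arm, 0.73 points would be:

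- SD 2: 0.37 SD, power 97%
- SD 3: 0.24 SD, power 72%
- SD 5: 0.15 SD, power 33%

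**3. What the sample can detect on a score.** Expected number analysed: 315 × 0.70 = 220.5, about 220 per arm. This is below both stated requirements (226 and 267).

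- 90% power: 3.2415 × √(2/220) = 0.31 SD
- 80% power: 2.8016 × √(2/220) = 0.27 SD

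These hold for one scale at a time, unadjusted for baseline and at an unadjusted two-sided 0.05.

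**4. The 267.** For two independent proportions, with mean p̄ = 0.105:

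- n = [1.960 × √(2 × 0.105 × 0.895) + 0.8416 × √(0.13 × 0.87 + 0.08 × 0.92)]² / 0.05² = (0.8497 + 0.3637)²/0.0025 = 589 per group.
- Alternatives: 629 with continuity correction, 586 unpooled, 582 by arcsine, 464 one-sided. None gives 267.
- A one-sample two-sided test of 13% against a fixed 8% gives [1.960 × √(0.08 × 0.92) + 0.8416 × √(0.13 × 0.87)]²/0.05² = 265.5, or 266. That is close to 267, but the article does not say how 267 was obtained.

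Power for the two-arm comparison is Φ[(0.05√n − 0.8497)/0.4321]:

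- n = 267: Φ(−0.076) = 47%
- n = 220: Φ(−0.250) = 40%

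**5. Calculations against outcomes.**

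- Primary: the calculation uses 0.73 in treatment beliefs on an unnamed scale; the outcomes are three DSS subscales, three SSDS subscales and the MSPSS.
- Secondary: the calculation uses a prevalence; the outcome is a GHQ-28 subscale score without a threshold.

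**The case against.** **The powered outcome may be a listed one.** The DSS beliefs subscale is a listed primary measure, and the 0.73 may have been meant for it. Neither the items of that subscale nor the source of the 0.73 can be seen here. A reader might infer that no listed scale measures what was powered, but the documents do not show that. What stands is narrower: the article does not make the link, and even if it were made, the calculation would cover at most one of seven primary measures.

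**Suicidal ideation is a listed secondary outcome.** The mismatch is one of metric, and the construct is the same. Nor does a score analysis need a cut-off, so the inference that one will be chosen after the data are seen is speculation. Any binary version could be defined in an analysis plan that is not shown. Even so, the article itself states both the calculation and the outcome, and the two differ.

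**The continuous outcomes may be well enough powered.** Detecting 0.27 to 0.31 SD is respectable. If the GHQ-28 score were normal with equal spread in both arms, a fall from 13% to 8% above a threshold would be a shift of z(0.92) − z(0.87) = 1.405 − 1.126 = 0.28 SD. That needs 203 per arm for 80% power and has about 83% at 220. The documents give no means of checking that distribution, but the argument rightly blocks the conclusion that the trial is underpowered on every outcome.

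**A journal article condenses.** The instrument and SD may be in the full protocol. That excuses brevity, but not a closing sentence that asserts a property the stated calculations do not establish.

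**Conclusion.** The point holds as a mismatch between calculations and outcomes. The 0.73 is tied to no listed primary measure, unit or SD. Ideation is sized as a prevalence but defined as a score. The assertion of adequate power for both primary and secondary outcomes is therefore unsupported as written.

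A reader might go further and conclude that power is inadequate throughout. The documents do not support that: for scores the gap is in the justification, and whether 0.27 to 0.31 SD is good enough depends on SDs and target differences that the article does not give. For a binary ideation outcome the shortfall can be shown: about 40% power at 220 per arm and 47% at 267, against 589 per arm needed for 80%.

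These figures assume two-sided 0.05, 1:1 allocation, 30% loss in each arm, normal approximations and one outcome at a time. A one-sided test would still need 464 per arm for 13% against 8%.

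**What to change.** 1. Name the primary subscale that the calculation is for. Restate it as a standardised detectable difference at the number expected to be analysed: with about 220 per arm, 0.31 SD at 90% power or 0.27 SD at 80%, two-sided 0.05, per single scale. If the 0.73 is kept, give its scale and SD.
2. Keep suicidal ideation as a GHQ-28 score and state its detectable difference in SD units.
3. If a binary version is kept instead, fix the cut-off in advance and state that power for 13% against 8% is about 40% at 220 per arm (about 47% at 267), and that about 589 analysed per arm would be needed for 80%. This option should not be adopted at the present N without that statement.
4. Withdraw the sentence claiming adequate power for both primary and secondary outcomes.

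The cost is rewording of the sample size and outcome text. N and data collection do not change.

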## Background

Males in the construction industry are at greater risk of suicide than those in the general working population [1]. The reasons underpinning the elevated risk of suicide among males in the construction industry are multifaceted, but likely involve poor help-seeking and high stigma against mental health issues. Evidence suggests for example that help-seeking rates for common mental health problems, including depression, are consistently lower in males compared to females [2]. Internalised stigma, or self-stigma, [3] and stoicism [4] may represent further barriers to help-seeking in males.

Due to the cyclical nature of construction work, males employed in the construction industry are also more likely to experience periods of unemployment than those in other industries [5]. This represents a further risk factor, as research consistently demonstrates that unemployment is associated with an elevated risk of mental health problems [6] and suicidal behaviour [1]. The experience of unemployment, and subsequent loss of the work-related role, social support, and sense of time structure and activity provided by employment [7], may compound feelings of self-stigma and shame associated with a mental health problem, further contributing to suicide risk. To some extent, the experience of unemployment in the construction industry is normalized, with workers anticipating periods without work as they move from project to project [8].

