## Methods

### Study design

Contact&Connect is an individual-level two-arm randomised controlled trial (Additioanl File 1). A total of 630 participants (315 in each arm) will be recruited. Simple randomisation using a random numbers table generated by computerised software (Stata for Windows, version 13 [13]) will be used to establish the randomisation sequence. Participants will be allocated to either the intervention or wait-list control group by an offsite researcher working independently from the research team. Owing to the nature of this intervention, neither the participants themselves nor the intervention team will be blind to allocation. However, outcome assessors will remain blind to treatment allocation through the use of unique study identifiers.

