### Participants

Males between the ages of 30 and 64 years who are registered with Incolink, and who own a smart phone with internet connectivity with adequate data download capacity will be invited to participate. Only unemployed persons contacting Incolink over the three months recruitment procedure will be considered.

Study exclusion criteria includes females, those younger than 30 years or older than 64 years, and those without a smart phone, internet connectivity, or adequate data download capacity, and those with inadequate English language skills.

Written informed consent will be sought from all participants prior to allocation. Ongoing consent will be inferred from participants’ response or non-response to the intervention materials and follow-up questionnaires.

Participants will be allocated to either the intervention or control group by an offsite researcher working independently from the research team.

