Limitations of this design include the potential confounding influence of reemployment. As reemployment is associated with improvements across a number of health domains, including reductions in mental ill health and depression symptomatology [30], the inclusion of individuals who were reemployed during the study may dilute any effect of the intervention package. However, it would be clearly inappropriate and unethical to request that participants refuse offers of employment during the 12 month intervention and follow-up period. Additionally, as the exclusion of these participants would have serious implications for statistical power, we decided to retain these individuals in all of our analyses. However, our analytic strategy will account for re-employment during the six month intervention period.

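### The 13% control rate behind the suicidal-ideation power claim is a working-population figure, carried over without justification to unemployed construction men

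*Protocol article*

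**What the plan says.** All of the sizing is in the Methods section printed as *Same size and power calculations*. For suicidal ideation, a secondary outcome, the reference rate is introduced with "our previous study has shown that 13 % of the working population report suicide ideation". The effect follows: "We believe it is realistic to expect a change from 13 % to 8 % prevalence following the trial". The result is then given: "Power calculations indicate we will need 267 persons per group to detect this difference at the nominal 0.05 significance level with 80 % power". After a 30% drop-out allowance the target is 630, which the section closes by calling sufficient for both the primary and the secondary outcomes. *Study design* confirms the split: "A total of 630 participants (315 in each arm) will be recruited".

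The people recruited are a different group from the one that supplied the 13%. *Participants* says "Only unemployed persons contacting Incolink over the three months recruitment procedure will be considered". *Background* states that men in construction have a higher suicide risk than the general working population, and adds that "research consistently demonstrates that unemployment is associated with an elevated risk of mental health problems [6] and suicidal behaviour [1". The secondary objective in *Study objectives and outcomes* places the ideation comparison at 12 months after enrolment, against wait-list.

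**The concern.** The trial's rationale is that these men differ from the general working population in mental health risk, yet the power calculation treats the two as having the same ideation rate. A reader would expect either a rate for unemployed men or a sentence explaining why the working-population rate is a fair stand-in. The article has neither.

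The rate that matters is the wait-list rate at 12 months, and the document gives reasons why that may differ from the rate at entry. The Discussion says that "reemployment is associated with improvements across a number of health domains, including reductions in mental ill health and depression symptomatology", *Statistical methods* expects some participants to find work, and *Control condition* gives wait-list men the materials once the intervention period ends, which is before the 12-month assessment.

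Power for a difference in proportions depends on the control rate and on whether the absolute or the relative reduction is held fixed when that rate changes. The article fixes the first without support and does not address the second. What is at stake is whether the stated power describes the trial being run.

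**Working it through.** **Inputs from the article:** control 13%, intervention 8% (difference d = 0.05, ratio 8/13 = 0.615), alpha 0.05 with sidedness not stated, stated n = 267 per group for 80% power, 315 per arm, 30% drop-out. Completers per arm: 315 × 0.70 = 220.5, taken as 220.

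**Assumed input:** the article gives no ideation rate for unemployed construction men, so control rates of 16%, 18% and 20% are used as an illustrative range.

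**Formulas** (two-proportion z-test, 1:1, pooled variance under the null; p̄ is the mean of p₁ and p₂):

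- n per arm = [z₁₋α/₂ √(2p̄(1−p̄)) + z₁₋β √(p₁(1−p₁) + p₂(1−p₂))]² / d²
- power = Φ{[d√n − z₁₋α/₂ √(2p̄(1−p̄))] / √(p₁(1−p₁) + p₂(1−p₂))}

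**Step 1: the plan's own figure.** For 13% versus 8%, p̄ = 0.105. The null term is 1.960 × √(2 × 0.105 × 0.895) = 0.8497. The alternative term is 0.8416 × √(0.1131 + 0.0736) = 0.8416 × 0.4321 = 0.3637. So n = (1.2134 / 0.05)² = 588.9, or 589 per arm. The stated 267 is not reproduced. A one-sided test needs 464, a two-sided test with continuity correction 629, and the unpooled and arcsine versions 587 and 583 two-sided.

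**Step 2: power at 13% versus 8%, two-sided.**

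- n = 220: (0.7416 − 0.8497) / 0.4321 = −0.250, power 40%
- n = 267: (0.8170 − 0.8497) / 0.4321 = −0.076, power 47%
- n = 315: (0.8874 − 0.8497) / 0.4321 = 0.087, power 53%

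**Step 3: change the control rate, two-sided.** Worked example at 20% and n = 220:

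- 5 points kept (20% vs 15%): (0.7416 − 1.0532) / 0.5362 = −0.581, power 28%
- ratio 8/13 kept (20% vs 12.3%): (1.1410 − 1.0200) / 0.5176 = 0.234, power 59%

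| Control rate | Effect held | 220 per arm | 267 per arm | 315 per arm |
|---|---|---|---|---|
| 13% | 13% vs 8% | 40% | 47% | 53% |
| 16% | 5 points | 33% | 39% | 45% |
| 18% | 5 points | 30% | 36% | 41% |
| 20% | 5 points | 28% | 33% | 38% |
| 16% | ratio 8/13 | 49% | 56% | 63% |
| 18% | ratio 8/13 | 54% | 62% | 69% |
| 20% | ratio 8/13 | 59% | 68% | 75% |

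**Step 4: how far the result holds.** A higher control rate lowers power when the absolute difference is kept and raises it when the ratio is kept. No cell in the table reaches 80%. Two cases outside the table do:

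- Control rate 30% with the ratio kept gives 81% at 220 per arm, two-sided.
- Control rate 20% with the ratio kept, no drop-out and a one-sided test gives (1.3653 − 1.645 × 0.5204) / 0.5176 = 0.984, power 84%. With 220 completers the same one-sided case gives (1.1410 − 0.8560) / 0.5176 = 0.551, power 71%.

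**The case against.** The strongest reply is that the article never says ideation exceeds 13% in this group. Its Background speaks of suicide, mental health problems and suicidal behaviour, not of ideation prevalence, and also remarks that spells without work are to some extent expected in construction. The source of the 13% is not at hand, so it cannot be checked whether the working population there means employed people, the labour force or working-age adults. Re-employment could also bring a higher entry rate down to about 13% by 12 months. All of this stands. It rules out saying that 13% is wrong, but it does not supply the missing justification.

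Three stronger readings are tempting, and the document does not support them.

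- A reader might infer that the borrowed rate by itself makes the trial underpowered. It does not, because the direction depends on which effect measure is held fixed.
- A reader might take the expected change from 13% to 8% as a before-after effect. The next sentence counts persons per group and the objective is set against wait-list, so this is mostly loose wording.
- A reader might conclude that a null result could not be interpreted. It could, from the estimate and its confidence interval.

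It is also fair to say that this is a secondary outcome, that *Data collection* measures it by subscale scores and *Statistical methods* analyses it by regression, and that no estimate or type I error rate is affected. The two-proportion figures test the article's own power statement, and do not give the power of the planned regression.

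**Conclusion.** The point holds in a limited form. A working-population prevalence is used, without explanation, as the control rate for a trial of unemployed construction men whom the same article describes as at higher risk. The consequence for power is uncertain in direction. After the planned drop-out, the assumed 16% to 20% range moves power from about 40% down to between 33% and 28%, or up to between 49% and 59%.

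The 80% claim fails across that range and at 13% itself, with or without drop-out, on a two-sided 0.05 test. The larger cause is the separate arithmetic error, 267 where 589 per arm are needed. The control-rate question would remain after that correction, because 589 would still rest on an unsupported 13%. The conclusion rests on the assumed range, a two-sided test and analysis of completers.

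**What to change.** In *Same size and power calculations*:

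1. Justify 13% as the expected wait-list rate at 12 months in unemployed construction men, or replace it with a stated plausible range.
2. Word the effect as a between-arm difference at 12 months, and say whether the absolute or the relative reduction is held across the range.
3. Report power for the planned 630 after 30% drop-out across that range, stating whether the test is one- or two-sided.
4. Withdraw the 80% figure, and the closing statement that the sample is sufficient, for this secondary outcome.

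The cost is one recalculation and one rewritten paragraph. No extra recruitment is needed. The downside is that the stated power becomes a range and looks less favourable.

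### The 267 per group stated for detecting 13% versus 8% suicidal ideation with 80% power does not follow from its inputs: about 589 analysed per group are needed, and 267 gives about 47% power

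*Protocol article*

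**What the plan says.** Under the sample size heading, the protocol article gives a separate calculation for suicidal ideation, a secondary outcome. The starting prevalence comes from earlier work: "our previous study has shown that 13 % of the working population report suicide ideation". The target is a judgement: "We believe it is realistic to expect a change from 13 % to 8 % prevalence following the trial". The result is "we will need 267 persons per group to detect this difference at the nominal 0.05 significance level", with 80% power. The article does not say whether the test is one-sided or two-sided. It states no baseline correlation, pairing or covariate adjustment behind the figure.

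After allowing for 30% drop-out, it sets the target at 630 and describes recruitment over three months as "thus allowing us to obtain a sample size adequately powered to assess both primary and secondary outcomes".

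The Study design section fixes the comparison: "Contact&Connect is an individual-level two-arm randomised controlled trial", and "A total of 630 participants (315 in each arm) will be recruited".

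**The concern.** The two prevalences, the significance level, the power and the allocation are all in the article, so the figure of 267 can be checked directly. A five-point difference between prevalences near 10% usually needs well over 267 per group.

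This is the only secondary outcome with a calculation, and 267 is the larger of the two stated requirements (the other is 226 per group for the primary outcome). The claim of adequate power for secondary outcomes therefore rests on it. If the figure is wrong, readers may take a non-significant result on suicidal ideation as evidence that the intervention does nothing, when the trial had a poor chance of detecting the effect it was planned around.

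**Working it through.** **Inputs.** From the sample size section: p1 = 0.13, p2 = 0.08, alpha = 0.05, power 80%, stated n = 267 per group, drop-out 30%. From Study design: two individually randomised arms, 315 in each. Assumption: two-sided test, because sidedness is not stated; the one-sided result is also shown.

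**Step 1: required n.** For two independent proportions with pooled variance under the null, where p̄ = (0.13 + 0.08)/2 = 0.105:

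n = [z(α/2)·√(2p̄(1−p̄)) + z(β)·√(p1(1−p1) + p2(1−p2))]² / (p1 − p2)²

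- √(2 × 0.105 × 0.895) = 0.4335, and 1.96 × 0.4335 = 0.8497
- √(0.13 × 0.87 + 0.08 × 0.92) = 0.4321, and 0.8416 × 0.4321 = 0.3637
- n = (0.8497 + 0.3637)² / 0.0025 = 588.9, so 589 per group

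**Step 2: can 267 be reproduced?**

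| Calculation | n per group |
|---|---|
| Two-sided, pooled | 589 |
| Two-sided, unpooled | 587 |
| Two-sided, continuity-corrected | 629 |
| Two-sided, arcsine | 583 |
| Two-sided, log odds ratio | 601 |
| Two-sided, log risk ratio | 606 |
| One-sided 0.05, pooled | 464 |
| One-sided 0.05, continuity-corrected | 503 |
| Stated | 267 |

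No two-group version comes near 267. The nearest match is a one-sample test of 13% against a fixed null of 8%:

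[1.96·√(0.08 × 0.92) + 0.8416·√(0.13 × 0.87)]² / 0.0025 = 265.5, so 266.

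That may be where the figure came from, but it treats one prevalence as known without error and does not fit a trial that compares two randomised arms. With 13% as the fixed null, the one-sample result is 316.

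**Step 3: power at the sizes the trial could have.** Power = Φ{[(p1 − p2)√n − z(α/2)·√(2p̄(1−p̄))] / √(p1(1−p1) + p2(1−p2))}.

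- n = 267: (0.05 × √267 − 0.8497)/0.4321 = −0.076, so power is 47.0%. Exact enumeration of the two-sided chi-square test gives 47.1%.
- n = 315 (everyone analysed): (0.05 × √315 − 0.8497)/0.4321 = 0.087, so power is 53.5%.
- n = 220 (315 × 0.70 = 220.5): (0.05 × √220 − 0.8497)/0.4321 = −0.250, so power is 40.1%.

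A one-sided test at 267 would have 59.5% power.

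**Step 4: what could be detected with 80% power.** Solving the Step 1 formula for p2 with p1 = 0.13 gives a fall to about 5.9% at 267 per group, 6.4% at 315 and 5.3% at 220.

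**Step 5: what else would be needed to reach 267.** The post-trial prevalence would have to be about 6% (n = 275), or an adjusted analysis would need a baseline correlation of about √(1 − 267/589) = 0.74. The article states neither.

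**The case against.** The arithmetic is hard to contest, but its reach can be.

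*The planned analysis may not be the one calculated.* The Data collection section measures suicidal ideation by scores on the GHQ-28 suicidality subscale, and the Statistical methods section plans regression. A score analysis could have more power than a comparison of prevalences. This stands. A reader might infer that the trial is underpowered for suicidal ideation however it is analysed, but the article does not support that, because it gives no score difference or standard deviation. The shortfall is shown for the prevalence comparison only.

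*The other secondary outcomes are also scores.* The same limit applies to the CESD-R and the BSI depression subscale. With 220 per arm, 80% power is reached at a standardised difference of about (1.96 + 0.8416) × √(2/220) = 0.27, which may or may not be enough. Their power is unjustified in the article; it is not shown to be inadequate.

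*With full retention, power exceeds one half.* This is also true. It would be too strong to say that an effect of the planned size would always be missed more often than found. That holds at 267 (47%) and after the planned drop-out (40%), but not at 315 (53%). Intention-to-treat analysis with imputation could bring the nominal number to 315, although imputation does not restore all the lost information.

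*It is a secondary outcome.* The primary-outcome requirement of 226 per group and the validity of the design are untouched. That limits the consequence, but the article still makes an explicit power claim that rests on this figure.

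**Conclusion.** The stated 267 per group is wrong for the comparison described. The article's own inputs require about 589 analysed per group two-sided, so 267 is 45% of what is needed (267/589 = 0.45). Even a one-sided test needs 464. Power for 13% versus 8% is 40% to 53% across the realistic range of analysed numbers, not 80%. The claim of adequate power for secondary outcomes is false for this prevalence comparison and unsupported for the GHQ-28, CESD-R and BSI scores.

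The conclusion assumes independent arms, 1:1 allocation, no clustering and an unadjusted comparison. The first three follow from the Study design section; the last reflects the absence of any stated adjustment behind the figure. The conclusion does not depend on sidedness or on the choice among standard two-group formulas.

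**What to change.** Keep the target of 630 and correct the sample size section:

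- Replace the 267 per group at 80% power with a requirement of about 589 analysed per group for 13% versus 8% (two-sided 0.05), and state the sidedness.
- State that the roughly 220 per group expected after drop-out give about 40% power for that difference, and 80% power only for a fall from 13% to about 5.3%.
- Withdraw the statement that the sample is adequately powered for secondary outcomes.
- Commit to reporting the suicidal ideation effect with a confidence interval, so that a null result is not read as evidence of no effect. Suicidal ideation can remain a secondary outcome if its low power is disclosed.

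Adjusting for the baseline GHQ-28 suicidality score could recover some precision, but only if that score is collected at baseline. The Data collection section does not list it among the baseline content, so this would need confirmation or an added instrument.

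Apart from that option, the cost is rewording and a less favourable stated power. No extra participants are needed. The article says full enrolment had not yet begun, so the correction could be made before it started.

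If 80% power for 13% versus 8% were wanted instead, the trial would need 589/0.7 = 842 per group, or 1,684 in total.
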